### Sample size

2.4

Given that this study is a pilot RCT, its primary focus is on evaluating the feasibility and practical implementation of the AI-HEALS intervention. Therefore, it is not designed to perform statistical hypothesis testing but rather to collect preliminary data on intervention operability and acceptability. As such, the sample size estimation for this pilot RCT does not follow traditional power analysis methods used for hypothesis testing. Instead, a pragmatic rule of thumb was applied to select a sample size sufficient to determine outcome variability and identify any operational issues (27). In line with the suggestions put forward by Billingham et al., the sample size for this pilot study is set at around 25 participants per group, amounting to a total of 50 participants (27). Anticipating an attrition rate of 20%, we determined that a minimum total sample of 60 participants (30 per group) would be necessary.

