**Clinical trial registration:**

The study is scheduled to begin in April 2025 and is expected to conclude in December 2026. This research protocol is the first version and was registered with the China Clinical Trial Registration Center on February 14, 2025 (Registration Number: ChiCTR2500097233).

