### Randomization and blinding

2.2

In this study, the randomization procedure uses a computer-generated sequence of random numbers. Patients will be assigned to the intervention and standard care groups in a 1:1 ratio. This randomization process will take place prior to patient admission. The aim is to ensure that each patient is assigned to the appropriate study group in a predefined order, thus ensuring randomization and fairness of allocation. When patients are admitted to the hospital, they will be assigned a unique code. This code is consistent with the sequence of random numbers and ensures smooth and consecutive enrollment of patients. Once randomization is complete, patients are directed to the appropriate hospital room based on their grouping. Specifically, patients in the intervention group are sent to Ward A, while those in the control group are sent to Ward B to prevent any possible cross-talk between the different interventions.

To ensure the confidentiality of the allocation sequence, an independent team member will be responsible for the randomization process and be neither involved in participant registration nor in intervening in the allocation. This is to prevent disclosure of the sequence during the course of the study. This team member then forward the allocation results to the intervention team. By doing this, both the participant enrollment team and the intervention team know nothing about the allocation in advance.

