### Study sample

2.3

This research will adopt a continuous enrollment method to recruit families of children diagnosed with asthma from April 2025 to December 2026. The detailed inclusion and exclusion criteria are as follows:

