### Recruitment

2.5

This study endeavors to recruit families of children with asthma who satisfy the inclusion and exclusion criteria at the target hospital. The recruitment process will be spearheaded by the hospital’s medical team. They will identify and extend invitations to eligible patients when they are admitted to the hospital. Subsequently, the research team will carry out an initial face-to-face communication with the patients. During this communication, detailed information about the study’s objectives, procedures, potential benefits, and possible risks will be provided. Eligible patients will be invited to the hospital for a thorough health assessment. This assessment includes a detailed review of the child’s asthma history and symptoms. After making certain that the patients have a full understanding of the study and answering any questions they might have, the families of children with asthma will be requested to sign an informed consent form. Only those who sign the informed consent form will be formally enrolled in the study.

Participants will receive a three-month AI-HEALS intervention. Additionally, this study employs fixed measurement agents to ensure reliability of self-report measures. Specifically, the same family member who initially accompanied the child to the first hospital visit will be designated to complete all self-report assessments throughout the study period to maintain measurement consistency. To encourage maximum participation, as an incentive for their involvement, all participants will receive a free medical consultation after the study.

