#### Primary outcomes

2.9.1

The primary outcome was changes in asthma symptom control, measured using the Childhood Asthma Control Test (C-ACT) at baseline, discharge, and post-intervention. Given the nested longitudinal structure of repeated measurements within families, we employed multilevel negative binomial models to analyze asthma symptom frequency (count data), estimating incidence rate ratios (IRRs) and 95% confidence intervals (CIs).

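### Sixty enrolled leaves 48, not 50, at 20% attrition, and recruitment is dated to end in the same month as a study whose primary outcome needs three months of follow-up

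*Protocol article*

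**What the plan says.** Section 2.4 (Sample size) does not use a power calculation. It states that "a pragmatic rule of thumb was applied to select a sample size sufficient to determine outcome variability and identify any operational issues", and that "the sample size for this pilot study is set at around 25 participants per group, amounting to a total of 50 participants". It then allows for losses: "Anticipating an attrition rate of 20%, we determined that a minimum total sample of 60 participants (30 per group) would be necessary". Section 2.2 fixes equal allocation: "Patients will be assigned to the intervention and standard care groups in a 1:1 ratio".

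On dates, section 2.3 (Study sample) plans to "recruit families of children diagnosed with asthma from April 2025 to December 2026". The registration paragraph of the abstract says: "The study is scheduled to begin in April 2025 and is expected to conclude in December 2026".

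On follow-up, section 2.5 says: "Participants will receive a three-month AI-HEALS intervention". Section 2.9.1 has the primary outcome "measured using the Childhood Asthma Control Test (C-ACT) at baseline, discharge, and post-intervention", and Table 1 places the last C-ACT at 3 months. The article states no earlier close of enrolment and no follow-up after December 2026.

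**The concern.** An attrition rate is a share of those enrolled. To keep a target number, the target is divided by one minus the rate. The figure of 60 does not meet that test, yet it is called the minimum necessary. A reader who relies on section 2.4 will expect 50 children with final data at 20% loss, and the stated inputs do not give that.

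The dates raise a separate problem. If recruitment can run to the last month of the study, the final recruits have no room for a three-month programme and its closing measurement. Those primary outcomes would be missing because of the calendar and not because families withdrew. Section 2.6 uses the word attrition for withdrawal, and nothing indicates that the 20% was meant to cover calendar losses as well. At stake are the accuracy of a stated planning figure and, depending on accrual, some three-month C-ACT scores.

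**Working it through.** **Inputs.** Target 25 per group, 50 in total; attrition 20%; enrolment 60, 30 per group (all section 2.4). Allocation 1:1 (section 2.2). Recruitment April 2025 to December 2026 (section 2.3). Study end December 2026 (registration paragraph). Intervention three months (section 2.5). Last C-ACT at 3 months (Table 1).

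**1. Reproducing the plan's figure.** Multiplying by one plus the rate gives 50 × 1.20 = 60 and 25 × 1.20 = 30, which match exactly. The article shows no formula, so this route is an inference.

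**2. What 60 yields.** Completers = enrolled × (1 − attrition): 60 × 0.80 = 48 in total and 30 × 0.80 = 24 per group.

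**3. What the target needs.** Enrolled = target / (1 − attrition): 50 / 0.80 = 62.5, so 63 in total; 25 / 0.80 = 31.25, so 32 per group and 64 in total with equal groups.

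**4. What attrition 60 supports.** 1 − 50/60 = 16.7%.

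**5. Chance of meeting the target.** If children drop out independently with probability 0.20 (an assumption), the chance of at least 25 completers is 43% in one group of 30 and 18% in both groups. The chance of at least 50 of 60 overall is 32%.

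**6. Effect on precision.** The 95% half-width for a difference in means, in SD units, is t × √(2/n), with 2n − 2 degrees of freedom:
- n = 25: 2.011 × √(2/25) = 0.569
- n = 24: 2.013 × √(2/24) = 0.581

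The increase is about 2%.

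**7. The calendar.** April to December 2025 is 9 months and January to December 2026 is 12, so recruitment spans 21 months. Counting three months back from the end of December 2026 gives the end of September 2026. If the three months run from discharge and not from enrolment, the cut-off is earlier by the length of the hospital stay.

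**8. How many children could be affected.** Accrual is not given, so this is a range:
- All 60 enrolled by the end of September 2026 (18 months, 60/18 = 3.3 per month): none affected.
- Even accrual over 21 months (60/21 = 2.9 per month): 60 × 3/21 = 8.6, about 9 of 60.

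Under even accrual, with 20% attrition among the rest, (60 − 8.6) × 0.80 = 41.1, or about 20.6 per group, with a half-width of about 0.63 SD. Moving the cut-off from two to four months before the study end takes this from 21.7 to 19.4 per group.

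**The case against.** The strongest reply is that no design property fails at 24 per group. The target is approximate, it rests on a rule of thumb, and section 2.4 says the trial is not designed for hypothesis testing. No significance level, power or effect size enters the number. Sixty is also described as a floor, so the team may enrol more. All of this stands, and it makes the first part small. It does not make 60 the minimum that 50 completers and 20% attrition imply.

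On the dates, the recruitment sentence may simply repeat the overall study period, and the December 2026 end is only an expectation. Filling 60 places by the end of September 2026 needs 3.3 children per month instead of 2.9, after which the overlap costs nothing. Section 2.12 plans intention-to-treat analysis with multiple imputation, and a late recruit would still contribute baseline and perhaps discharge C-ACT scores. These points limit the likely loss. They do not reconcile the two dates, and imputation does not replace a three-month score that the schedule left no time to observe.

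A reader might go further and infer that the trial misses a required 25 per group, or that about 41 children with final data is the yield to expect. The documents support neither. The 25 is an approximate aim and not a threshold, and the 41 depends on even accrual over the full 21 months, which the article does not state.

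**Conclusion.** The point holds in two limited parts. The enrolment figure in section 2.4 is inconsistent with its own inputs: 60 at 20% attrition gives 48, and 50 would need 63, or 64 with equal groups. The certain consequence is one child per group and about 0.01 SD of half-width, which is minor for a pilot of this kind.

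The dates in section 2.3 and the registration paragraph conflict with a three-month primary measurement. Followed as written, they would leave any child enrolled after about September 2026 without that measurement inside the study period. This is the weightier part, but its size is conditional: from no children to about 9 of 60 across the two accrual patterns examined. The conflict itself rests only on stated dates and the stated follow-up. The count rests on an accrual assumption.

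**What to change.** In section 2.4, state that 60 enrolled gives about 48 children with three-month data (24 per group) at 20% attrition, or that 60 keeps 50 if attrition is no more than 16.7%. Enrolling 64 would also resolve it (32 × 0.80 = 25.6 expected per group), but the small shortfall does not demand this.

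Reconcile section 2.3 with the registration paragraph. Either close enrolment before the study end by at least the hospital stay plus three months, or move the study end so that it follows the last enrolment by that interval. Say whether the three months are counted from enrolment or from discharge, since this sets the cut-off.

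The cost is a reworded sentence in section 2.4 and one changed date, with no extra patients. The date should be settled before late recruits enter, because a missed three-month assessment cannot be recovered afterwards.

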### Recruitment

2.5

This study endeavors to recruit families of children with asthma who satisfy the inclusion and exclusion criteria at the target hospital. The recruitment process will be spearheaded by the hospital’s medical team. They will identify and extend invitations to eligible patients when they are admitted to the hospital. Subsequently, the research team will carry out an initial face-to-face communication with the patients. During this communication, detailed information about the study’s objectives, procedures, potential benefits, and possible risks will be provided. Eligible patients will be invited to the hospital for a thorough health assessment. This assessment includes a detailed review of the child’s asthma history and symptoms. After making certain that the patients have a full understanding of the study and answering any questions they might have, the families of children with asthma will be requested to sign an informed consent form. Only those who sign the informed consent form will be formally enrolled in the study.

Participants will receive a three-month AI-HEALS intervention. Additionally, this study employs fixed measurement agents to ensure reliability of self-report measures. Specifically, the same family member who initially accompanied the child to the first hospital visit will be designated to complete all self-report assessments throughout the study period to maintain measurement consistency. To encourage maximum participation, as an incentive for their involvement, all participants will receive a free medical consultation after the study.

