Assess the extent to which a three-month intervention program grounded in the AI-HEALS improves clinical outcomes in childhood asthma patients’ physiological indicators.Evaluate how effectively the three-month comprehensive intervention program can improve the psychological indicators of the parents of children with asthma.Ascertain the effectiveness of the three-month comprehensive intervention program in promoting self-management behaviors among the parents of children with asthma.

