#### Inclusion criteria

2.3.1

Age range: The children should be between 6 and 13 years old.Diagnostic criteria: Children enrolled in this study must be diagnosed with asthma by a specialized pediatric pulmonologist and currently receiving standardized treatment. The diagnostic criteria are based on two components: 1) clinical manifestations including recurrent wheezing, cough, and shortness of breath (particularly exacerbated at night or post-exercise) (26); and 2) objective pulmonary function test results demonstrating reversible airflow limitation. Specifically, for children with recurrent cough and/or wheezing: forced expiratory volume in one second (FEV_1_) must be <80% of predicted value with an FEV_1_/forced vital capacity (FVC) ratio <0.8, and following inhalation of a short-acting β_2_-agonist, FEV_1_ increases by ≥12% and absolute improvement ≥200 mL (26). Children not meeting both diagnostic components will be excluded after physician confirmation.Parental involvement: The child’s primary caregiver must be willing and capable of participating in all study-related activities, including uploading daily life records (e.g., medication adherence logs, physical activity records), engaging in interactive health consultations with AI-HEALS, receiving and reviewing health education articles delivered by the system, and completing all study assessments.Technology requirements: The parents must possess a smartphone that can access WeChat and be willing to utilize the platform to receive and reply to the intervention content of the study.

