### Questionnaires

2.11

Childhood Asthma Control Test (C-ACT): The C-ACT is an important tool for measuring how well asthma symptoms are controlled in children. It has two parts with a total of seven questions in Chinese version. The first part has four questions for the child to answer. Each question is scored from 0 to 3, based on how the child feels about their asthma control. The second part has three questions for the parent to answer. Each question is scored from 0 to 5, based on how often the child has asthma symptoms in the last four weeks. The total score of the C-ACT goes from 0 to 27. A score of 23 or higher means asthma is fully controlled, with few symptoms affecting daily life. A score between 20 and 22 means partial control, where symptoms are somewhat managed, but some problems remain. A score of 19 or less means asthma is not controlled, and stronger treatments may be needed (31).Short-Form Egna Minnen av Barndoms Uppfostran for Chinese (s-EMBU-C): The s-EMBU-C is a questionnaire designed to evaluate how children see their parents’ parenting styles. The child fills out this questionnaire. There are separate versions for fathers and mothers. Each version has 21 questions, divided into three parts: rejection (6 items), emotional warmth (7 items), and overprotection (8 items). The questions are scored using a scale from 1 to 4. “Never” gets 1 point, “Occasionally” gets 2 points, “Frequently” gets 3 points, and “Always” gets 4 points. Item 15 is scored in reverse. The scores for each part are found by adding up the points for each question in that part. A higher score in a part means the parent shows that parenting style more often. The total score for both versions can range from 28 to 112 points (32).The assessment of depression and anxiety will use the Chinese version of the Patient Health Questionnaire-4 (PHQ-4). This is a short self-report tool to check depression and anxiety symptoms over the past two weeks. The PHQ-4 has four questions. The first two questions focus on depression symptoms, and the last two focus on anxiety symptoms. Each question is rated on a scale from 0 to 3: “Not at all” (0 points), “Several days” (1 point), “More than half the days” (2 points), and “Nearly every day” (3 points). The total score goes from 0 to 12. In studies in China, the PHQ-4 has shown high validity and reliability, with a Cronbach’s alpha of 0.833 (33).The Chinese version of the Perceived Social Support Scale-Short Form (PSSS-SF) is used to measure the level of social support a person feels they receive. The scale has three questions, each about a different type of support: family support (Item 1), friend support (Item 2), and other support (Item 3). Each question is scored on a 7-point scale from 1 (Strongly Disagree) to 7 (Strongly Agree). The total score can range from 3 to 21. Higher scores mean more social support, showing that the person’s social network provides more help, both emotionally and practically (34).The Chinese version of the New General Self-Efficacy Scale (NGSES-SF) is used to measure a person’s confidence in their ability to succeed in tasks or face challenges. It has three questions, each focusing on a different aspect of self-efficacy. Item 1 looks at how capable a person feels in handling a situation. Item 2 focuses on how confident a person is in their skills. Item 3 looks at how confidence in one area can apply to other areas. The NGSES-SF uses a 5-point Likert scale. Respondents can choose from 1 (Strongly Disagree), showing low confidence, to 5 (Strongly Agree), showing high confidence. The total score can range from 3 to 15 (35).The Chinese version of the EQ-5D-5L scale (EuroQol-5 Dimensions 5 Levels) will be used to measure quality of life. The scale looks at five important health areas: mobility, self-care, usual activities, pain/discomfort, and anxiety/depression. For each area, there are five levels, ranging from “no problems” to “extreme problems.” This lets respondents choose the level that best matches their condition. It gives a complete view of a person’s health in these five areas. The EQ-5D-5L also includes a Visual Analogue Scale (VAS). This part lets participants rate how they feel about their current health on a scale from 0 to 100. A score closer to 0 means worse health, while a score closer to 100 shows better health (36).Smoking behavior will be assessed using a self-designed questionnaire. The questionnaire has four multiple-choice questions to categorize smoking habits. These questions are meant to find out: whether the person smokes, how long it has been since they quit smoking (if they quit), how many cigarettes they smoke daily, and when they started smoking. The first question is “Do you have a smoking habit?” with these options: (1) Yes, I smoke regular cigarettes; (2) Yes, I smoke e-cigarettes; (3) I smoke both; (4) I used to smoke (now quit); (5) I have never smoked. Based on their answers, participants will be grouped into two categories: smokers, which include people who currently smoke regular cigarettes, e-cigarettes, or both; and non-smokers, which include those who have never smoked and those who have quit smoking (37).Alcohol consumption will be evaluated using a self-developed 7-item multiple-choice questionnaire designed to assess: 1) current/historical alcohol use status, 2) age of drinking initiation, 3) age of drinking cessation (if applicable), 4) preferred alcoholic beverage types, 5) average daily alcohol intake, 6) pre-quitting daily consumption volume, and 7) perceived anxiety related to alcohol cessation. The instrument begins with the core screening question: ‘Which best describes your alcohol consumption pattern?’ Respondents choose from four mutually exclusive categories: (1) Never consumed alcohol; (2) Current regular drinker; (3) Former drinker who has quit; (4) New-onset drinker in the past year (43, 44).The Chinese version of the Pittsburgh Sleep Quality Index Short Form (PSQI-SF) is a shorter version of the Pittsburgh Sleep Quality Index, made to measure sleep quality. The scale has six items, covering five key aspects of sleep. Items 1 and 2 measure sleep efficiency. Item 3 measures how long it takes to fall asleep. Item 4 looks at sleep duration. Item 5 checks for sleep disturbances. Item 6 looks at overall sleep quality. The total score on the PSQI-SF goes from 0 to 15. A higher score means worse sleep quality (38).The Chinese version of the Family Communication Scale Short Form (FCS-SF) is made to measure how well family members communicate. The scale has four items that assess family communication. It uses a 5-point Likert scale, where 1 means “strongly disagree” and 5 means “strongly agree.” The total score goes from 4 to 20. A higher score means better communication among family members (39).The Chinese version of the Electronic Health Literacy Scale (eHEALS) measures how well parents of children can search for, evaluate, and use electronic health information to solve health problems. The scale has five items in one dimension. It uses a 5-point Likert scale, where 1 means “strongly disagree” and 5 means “strongly agree.” The total score ranges from 5 to 25. A higher score means better electronic health literacy (40).

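### Sections 2.3.1, 2.5 and 2.11 name different respondents for the self-reports, so parental outcomes may be measured in someone other than the caregiver who uses AI-HEALS

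*Protocol article*

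**What the plan says.** Three sections of the protocol article assign the respondent.

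- **2.5 Recruitment.** The stated aim is rater constancy: "this study employs fixed measurement agents to ensure reliability of self-report measures". The rule is that "the same family member who initially accompanied the child to the first hospital visit will be designated to complete all self-report assessments throughout the study". It does not require this person to be a parent, the primary caregiver or the AI-HEALS user.
- **2.3.1 Inclusion criteria.** "The child’s primary caregiver must be willing and capable of participating in all study-related activities". The activities listed include "engaging in interactive health consultations with AI-HEALS, receiving and reviewing health education articles delivered by the system, and completing all study assessments". Exposure and measurement are thus placed with the same person. A separate criterion requires the parents to have a smartphone with WeChat.
- **2.11 Questionnaires.** Some respondents are set by instrument. The child answers the first part of the C-ACT and the whole s-EMBU-C. For the C-ACT, "The second part has three questions for the parent to answer".

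The objectives and analysis are framed around parents. The second objective in the Introduction asks how well the program can "improve the psychological indicators of the parents of children with asthma", and the third concerns parents' self-management behaviors. Section 2.9.2 labels the behavioral and psychological outcomes as parental. Section 2.12 models parental outcomes with parent-level age and education as covariates.

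**The concern.** Keeping one rater per family is sound. The difficulty is that 2.5 selects the rater by who came with the child, while 2.3.1 selects by caregiving role and system use. These can be two people: a grandparent, or the parent who does not run daily care, may be the one who came first. Staff working from 2.5 and staff working from 2.3.1 could then hand the forms to different adults.

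Two things are at stake. First, the PHQ-4, NGSES-SF, PSSS-SF, EQ-5D-5L, B-PSQI and the smoking and alcohol forms would describe an adult who may have had little or no contact with AI-HEALS. If that adult is not a parent, the outcome label and the parent-level covariates would also not fit the person measured. Second, the parent items of the C-ACT ask about the child's symptoms over four weeks and need someone who saw the child in that time. Section 2.4 justifies the sample partly by what the pilot will show about outcome variability, so it matters whose outcomes are recorded.

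**Working it through.** No figure in the protocol depends on this rule, so there is none to reproduce. The check is a comparison of the text, followed by an illustration of size.

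**Step 1. Who answers, by section**

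| Measure | 2.5 | 2.3.1 | 2.11 and outcome labels |
|---|---|---|---|
| C-ACT part 1 | accompanying family member | primary caregiver | child |
| C-ACT part 2 | accompanying family member | primary caregiver | parent |
| s-EMBU-C | accompanying family member | primary caregiver | child |
| PHQ-4, NGSES-SF, PSSS-SF, EQ-5D-5L, B-PSQI, smoking, alcohol | accompanying family member | primary caregiver | parent (objectives, 2.9.2, 2.12) |

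The 2.5 and 2.3.1 columns follow from both sections speaking of all assessments. Every row therefore has at least two candidates. For the two child-completed rows, neither general rule fits 2.11. No section says that the accompanying person and the primary caregiver are the same.

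**Step 2. Share of the primary outcome that is affected**

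From 2.11, the child part is 4 items × 3 points = 12 and the parent part is 3 items × 5 points = 15. The total is 12 + 15 = 27, which agrees with the stated range. The parent part carries 15/27 = 56% of the maximum score.

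**Step 3. Illustration for the parental outcomes only**

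Let q be the share of families in which the respondent is not the AI-HEALS user. The protocol gives no value, so a range is assumed. Assume also that such respondents gain nothing and that the outcome variance is unchanged. Then:

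- observed effect = (1 − q) × effect in users
- sample needed for the same precision relative to the effect = 1/(1 − q)² times as large

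| q (assumed) | Families of 30 per arm | 1 − q | 1/(1 − q)² |
|---|---|---|---|
| 10% | 3 | 0.90 | 1.23 |
| 20% | 6 | 0.80 | 1.56 |
| 30% | 9 | 0.70 | 2.04 |
| 40% | 12 | 0.60 | 2.78 |

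The 30 per arm is the recruitment target in 2.4. If mismatched respondents benefit in part, the shrinkage is smaller. At q = 0 there is none.

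**Step 4. Why Step 3 does not carry over to the C-ACT**

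The C-ACT measures the child's control, and the child's family receives the intervention whoever fills in the form. A rater who sees less of the child reports less accurately, which is measurement error. It does not scale the effect by 1 − q.

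**The case against.** The strongest reply is that 2.5 concerns constancy only. Read together with 2.3.1, it may simply mean that the same caregiver should answer throughout. Families are approached at the child's admission and consent comes from parents or guardians (2.6), so the accompanying person may often be the primary caregiver. This has force. A reader might infer that the plan has settled on measuring someone other than the primary caregiver. It has not, because 2.3.1 makes that caregiver's completion of assessments an eligibility condition. What remains is a contradiction between two rules.

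A second reply is that AI-HEALS is directed at the family. Section 2.7.2 addresses parents and families, and nothing limits use to one adult, so a respondent who is not the main carer may still have used it. This also stands: lack of exposure is possible but not established.

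Third, 2.11 names the child or the parent for several instruments, and nothing says that 2.5 overrides it. That is correct, and it adds another conflict that needs resolving.

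Fourth, the rule is the same in both arms and rests on an event unrelated to the allocated arm, so it creates no spurious benefit. Section 2.4 also disclaims hypothesis testing, which limits the weight of any sample-size multiple. Both points are fair. They bear on the size of the problem, but they do not tell staff whom to give the forms to.

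**Conclusion.** The concern holds as an unreconciled conflict over the respondent. Section 2.5 is an explicit operating rule, so this is not a detail left to a fuller document. Followed literally, it allows parental outcomes to be taken from an adult who may not have used AI-HEALS and may not be a parent. The expected direction is toward no effect on those outcomes, with possible added reporting error in 15 of the 27 C-ACT points.

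The size is unknown. The factors of 0.90 to 0.60 rest on an assumed mismatch of 10% to 40% and on no benefit in mismatched respondents; neither has a basis in the protocol. A reader might infer that the pilot's estimates will be wrong, or that the primary effect will shrink by the same factor. The documents support neither: only mismatched families are affected, their number may be small or nil, and the dilution does not apply to the C-ACT. The point should be settled before enrolment, because a baseline taken from the wrong person cannot be recovered.

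**What to change.** In 2.5, replace the accompanying-person rule with wording such as:

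*One index caregiver per family, the primary caregiver described in 2.3.1, is named before allocation in both arms. This person uses AI-HEALS if the family is allocated to it, and completes all caregiver-reported measures and part 2 of the C-ACT at every scheduled assessment. The child completes part 1 of the C-ACT and the s-EMBU-C.*

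Record the index caregiver's relationship to the child, which is not among the sociodemographic variables listed in 2.10. If the index caregiver is not a parent, report the result as a caregiver outcome. Align 2.3.1 and 2.11 with the new wording.

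This keeps the constant rater that 2.5 seeks, and keeps the choice of rater independent of the arm. The cost is a short change to the text and one field on the form. The downside is that when someone else brought the child, the index caregiver has to be reached for the baseline forms.
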